•Objective 1: To determine the feasibility (i.e., rates of participant recruitment, enrolment, training compliance, retention/dropouts) of conducting the full randomised clinical trial.•Objective 2: To examine the safety of the administered interventions.•Objective 3: To explore the participants' perceptions regarding the study procedures, including the acceptability of interventions.•Objective 4: To explore Māori perceptions of how assessment and training practices in the trial are acceptable to cultural perspectives and values, including Te Ao Māori (a Māori worldview).•Objective 5: To derive the central tendency and variability of the clinical outcome measures to inform the sample size of a full clinical trial.

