### Allocation

After the baseline assessment, the participants will be allocated into one of the three study groups with equal probabilities. Blocks of unequal length, with the measurements and the possibilities of these lengths unknown to other investigators, will be used to promote allocation concealment. The senior biostatistician, using non-informative group allocation codes, will generate the allocation sequence using a standard computer software.

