### Allocation concealment

The allocation of groups will be concealed using opaque envelopes to conceal the sequence until interventions are assigned. The senior biostatistician will prepare the envelopes and provide them to the assistant research fellow (ARF). The ARF will give the opaque sealed envelope to the participants following the baseline assessment. The participants open the envelope to reveal the group they have been allocated to after the baseline assessment. The participants inform the ARF about the group, and the ARF administers one of the active interventions to the participant. If a participant is identified to be allocated to the usual care control group, they would be advised to continue managing their health condition as usual and attend the follow-up assessment sessions.

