### Outcome measures

The assistant research fellow will collect primary outcome measures throughout the study period. All secondary outcome measures will be collected at baseline, immediately post-intervention (4th week), and 3 months post-intervention by a research assistant (RA-2) blinded to group allocation. The RA will be adequately trained to collect quantitative sensory testing procedures, electrocardiogram, and electroencephalography recordings (Table 2).

**Table 2 T2:** Secondary outcome measures.

Outcome domain and constructs (96–98)	Brief description of measurement tools	Measurement time points
Pain		
Pain severity	The brief pain inventory—short form (pain subscale) Pain severity on a 10-point scale (0 = no pain and 10 = worst pain possible) in the past 24 h, 1 week, and 4 weeks.	T_B,_ T_1m,_ T_3m_
Pain unpleasantness	In the last 2 weeks, how unpleasant has your knee pain been? ‘Not at all’, ‘slightly’, ‘moderately’, ‘very much’, and ‘extremely’.	T_B,_ T_1m,_ T_3m_
Pain bothersomeness	In the last 2 weeks, how bothersome has your knee pain been? ‘Not at all’, ‘slightly’, ‘moderately’, ‘very much’, and ‘extremely’.	T_B,_ T_1m,_ T_3m_
Intermittent and constant pain	The measure of intermittent and constant osteoarthritis pain (11 items). Each item is rated on a 5-point ordinal response scale (Not at all/No constant or intermittent knee pain, Mildly, Moderately, Severely, Extremely).	T_B,_ T_1m,_ T_3m_
Pain quality	PainDETECT questionnaire (12 items). Each symptom is rated on a 5-point ordinal response scale (1 = never to 5 = very strongly). Score classification: ≤12—nociceptive pain, 13–18—possible neuropathic pain, ≥19—likely neuropathic pain.	T_B,_ T_1m,_ T_3m_
Movement evoked pain	Pain severity during a 6-min walk distance and physical performance tasks—rated pain on NPRS on a 0–100 scale (0 = no pain, 100 = the most intense pain imaginable) scale.	T_B,_ T_1m,_ T_3m_
Flare in osteoarthritis	Flare-OA (16 items) patient-reported instrument to assess the occurrence and severity of knee OA in the past 4 weeks.	T_B,_ T_1m,_ T_3m_
Physical functioning		
Pain interference	The brief pain inventory—short form (interference subscale—nine items) evaluate the impact of pain on daily activities Rated on a 10-point scale (0 = no pain and 10 = worst pain possible).	T_B,_ T_1m,_ T_3m_

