Sleep quality and disturbances	Pittsburgh sleep quality index (19 items) assesses sleep quality over a 1-month time interval. Scored 0 (no difficulty) to 3 (severe difficulty). Total score (range 0–21). Higher scores indicate worse sleep quality.	T_B,_ T_1m,_ T_3m_
The participants’ perceptions about interventions and their impact on their health condition/pain.		
Global perceived change	Perceived change in the knee pain when compared to baseline/before training (−5 = much worse, through 0 = unchanged, to +5 = completely, recovered).	T_1m, and_ T_3m_
Acceptability of interventions	Visual analogue scales (0–10) to measure overall acceptability, burden, perceived effectiveness, ethicality, culturally acceptable, research team's trustworthiness and knowledge, and the likelihood of negative side effects of training.	T_B_
Perceived treatment satisfaction and usefulness of training	Rated on a 0–10 NRS; 0—not at all satisfied to 10—highly satisfied.	T1m, and T3m
Credibility/expectancy of the intervention	The credibility/expectancy questionnaire (5 items)	T_B_
Predictors of training		
Level of engagement with the training	Rated on a 10-point ordinal items scale, where 1 = least engaged and 10 = highly engaged.	At every session
Level of motivation	Single-item; rated on a 10-point ordinal items scale, where 1 = least motivated and 10 = highly motivated.	T_B_ and every session
Cost-and-consequences		
Costs	The osteoarthritis cost-and-consequences questionnaire will be used to measure healthcare use/expenses in the past 3 months.	T_B,_ and T_3m_
Quantitative sensory testing, physical performance assessment and physiological recordings		
	Quantitative sensory testing procedures	T_B,_ T_1m,_ T_3m_
	Resting and evoked electroencephalography.	
	Heart rate, blood pressure, and respiratory rates	
	OARSI Minimum physical performance core set	
	Short physical performance battery (SPPB) standing balance tasks.	

T_B_, at baseline; T_1m_, immediately post-intervention (4th week); T_3m_, 3 months post-intervention.

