### Qualitative study

An assistant research fellow will coordinate with the investigators in conducting semi-structured in-depth interviews following the intervention to evaluate participant experiences in the trial (94, 95). As they finish the trial, the participants will be asked if they would consider this additional interview and be enrolled sequentially until numbers are met. The interview will explore experiences and perceptions regarding interventions based on the theoretical framework of acceptability. These would be recorded with the consent of the participants. The aims of this interview include exploring the participants’ experiences regarding the barriers and facilitators in participating in the trial. In addition, the interview aims to assess the acceptability of the research procedures, including the intervention, preferences for the study site, the perceived value of the study, and the acceptability of interventions as potential clinical treatments for managing knee OA. Furthermore, the interview seeks to explore the perspectives of Māori people on assessment and treatment practices that align with their cultural worldview (95). Māori is treated as an important subgroup and are selected and interviewed separately. We aim to interview five people per group with a purposeful sample of Māori participants from each group. The participants in the usual care group will also be interviewed to explore their experiences participating in the trial, including the acceptability of the assessment procedures.

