## Quantitative data analyses plan

Descriptive statistics will be derived for primary and secondary outcome measures. The sample size estimation was not determined for primary outcomes since it is a feasibility trial. However, we aim to recruit a sample (20 participants per group, 60 in total) in 1 year in a single centre to provide sufficient data for assessing adverse events, feasibility outcomes, identifying operational issues, and estimating variability estimates of clinical pain outcomes.

**In the full clinical trial**, linear mixed models will be used to examine the differences in changes in the pain and physical function between groups to determine the effectiveness of interventions against usual care based on the randomised group (i.e., using an intention-to-treat approach). Group–time interactions will be used to assess between-group differences at 1 and 3 months following the intervention, with 3 months being the primary endpoint. Potential explanatory factors (which could include age, sex, BMI, duration, baseline pain severity, and depression scores) will be adjusted in the analysis. In this feasibility study, we will still perform these analyses (with no stratification or competing exposure variables included) to assess the study protocol, focusing on the uncertainty in estimated effects, not statistical significance. The following parameters will be used to determine the sample size in the full clinical trial: standard deviations (SD) and correlations between repeated measures of outcome measures derived from the feasibility trial. The full trial will have 80% power to detect a meaningful difference in the primary outcome (i.e., pain severity at 3 months). The minimal clinically important difference for pain severity (NPRS) is 1.8 using a two-sided (0.05) significance level. An attrition rate informed by the results of this feasibility study will be incorporated.

Qualitative data analysis (72): The interviews will be audio-recorded and fully transcribed. The General Inductive Approach will guide the analysis. The qualitative findings will provide important information regarding recruitment and retention in the trial and the acceptability of interventions. The results of the qualitative study will be published separately.

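### Table 2 schedules the acceptability scales at baseline only, before allocation and training, in conflict with the text, and the exit interviews leave out people who withdraw

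*Protocol article*

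**What the plan says.** Objective 3 (Introduction) is to explore participants' perceptions "regarding the study procedures, including the acceptability of interventions".

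The quantitative instrument is a set of 0–10 visual analogue scales in Table 2 (Outcome measures), used "to measure overall acceptability, burden, perceived effectiveness, ethicality, culturally acceptable", together with the team's trustworthiness and knowledge and the likelihood of negative side effects. The only time point in that row is T_B. The table footnote defines the codes as T_B "at baseline; T_1m_, immediately post-intervention (4th week); T_3m_, 3 months post-intervention".

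The paragraph that introduces Table 2 says something different: "All secondary outcome measures will be collected at baseline, immediately post-intervention (4th week), and 3 months post-intervention".

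On sequence, the Allocation section states: "After the baseline assessment, the participants will be allocated into one of the three study groups with equal probabilities". Allocation concealment adds: "The participants open the envelope to reveal the group they have been allocated to after the baseline assessment".

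On interviews, the Qualitative study section states: "As they finish the trial, the participants will be asked if they would consider this additional interview and be enrolled sequentially until numbers are met". Five per group is the target, with Māori participants selected purposefully. The stated purpose of the interviews includes barriers and facilitators to taking part, and the analysis section says: "The qualitative findings will provide important information regarding recruitment and retention in the trial and the acceptability of interventions".

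**The concern.** Whether the two trainings are acceptable is one of the questions the feasibility trial exists to answer. It appears in the abstract, in the list of feasibility questions and in Objective 3, and Objective 4 asks about it from a Māori perspective. The one instrument that scores acceptability by component is tabulated at a visit where nobody yet knows their arm or has had a session. Such a rating can say whether people expect the training to be burdensome or culturally acceptable. It cannot say whether they found it so. Cultural acceptability is a clear example: the protocol itself treats touching the head at EEG-NF sessions as sensitive, yet the item on cultural acceptability has no tabulated score after any session.

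The interviews could fill the gap, but their invitation rule reaches only people who finish. Those who leave are the natural informants on retention, which the interviews are meant to inform. At stake is the evidence used to decide what to change before the full trial.

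**Working it through.** The plan gives no figure of its own on this point, so the check sets the passages side by side and then counts.

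**1. What the scales can measure as tabulated**
- Acceptability scales: T_B only (Table 2).
- T_B is the baseline visit (Table 2 footnote).
- Allocation and opening of the envelope: after the baseline assessment (Allocation; Allocation concealment).
- Training: after allocation (Interventions).

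Every tabulated rating therefore precedes knowledge of the arm and any exposure. With 20 per group, the two trained arms hold 2 × 20 = 40 participants, and 0 of 40 have a scheduled post-training score on these scales.

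**2. Whether the text overrides the table**
- The Outcome measures paragraph puts all secondary outcomes at three time points.
- Table 2 departs from that in several rows: perceived change and satisfaction have no baseline, costs have no week-4 measurement, credibility/expectancy is baseline only, and engagement is rated at every session.
- The narrative under Secondary outcomes describes the scales just after a sentence about ratings following training, but gives the scales no time point.

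The table varies by row, so it looks like the operative schedule and the sentence like a summary. The document does not say which governs.

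**3. What other post-training evidence exists**
- Satisfaction and usefulness, 0–10, at week 4 and 3 months (Table 2).
- Perceived change in knee pain, at the same visits (Table 2).
- Engagement and motivation at every session (Table 2).
- Attendance, reasons for non-compliance, and retention (Feasibility data).
- Symptom checklist during training (Safety data; Discussion).
- Interviews built on an acceptability framework (Qualitative study).

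Of the scored items, none covers experienced burden, ethicality or cultural acceptability.

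**4. What interviewing only finishers leaves out**
- Planned interviews: 5 × 3 = 15 of 60 (25%); in the trained arms 10 of 40 (25%).
- At the 80% retention target: 0.80 × 20 = 16 finish per arm and 4 do not. Interviews cover 5/16 = 31% of finishers and 0 of 4 non-finishers.

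As a benchmark only, suppose five people per arm were drawn at random from all 20 allocated and all agreed. The chance of including at least one non-finisher is 1 − C(f,5)/C(20,5), where f is the number finishing and C(20,5) = 15,504:

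| Retention | f | C(f,5) | Chance of at least one non-finisher |
|---|---|---|---|
| 90% (assumed) | 18 | 8,568 | 45% |
| 80% (trial target) | 16 | 4,368 | 72% |
| 70% (assumed) | 14 | 2,002 | 87% |

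Under the stated invitation rule the chance is 0% in each row.

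**The case against.** A reader might infer that the trial cannot show whether the delivered trainings were acceptable. The documents do not support that. Objective 3 is exploratory, the interviews follow the intervention and address acceptability directly, and the other sources listed under step 3 are collected after exposure. Attendance, reasons for non-compliance and the per-session ratings also come from people who later stop. This argument stands. It limits the point to what goes unscored and who goes unheard in the interviews.

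A reader might also take pre-exposure measurement as a settled decision. The Outcome measures paragraph says otherwise, so the firm statement is that table and text conflict.

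The baseline rating has its own use. The Discussion names anticipated acceptability among the influences on recruitment, and an item on the likelihood of side effects suits a prospective question. Asking credibility and expectancy before treatment is likewise no fault. What is lacking is the matching later score.

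It is tempting to say the baseline scores must flatter the interventions. Nothing in the documents fixes a direction. The Discussion lists biomedical beliefs and time commitment as possible barriers to taking part, so anticipated ratings could equally be lower than experienced ones.

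On the interviews, Māori participants are selected purposefully, so places are not filled purely in order of finishing, and a poor attender who stays to the end can be invited. Retention is defined by completing the follow-up assessment, so some of the 4 in 20 may have had all their training. The four in usual care received no training to judge. These points soften the counts. They do not supply an invitation route for people who withdraw.

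**Conclusion.** The point holds at moderate severity. As tabulated, the acceptability scales capture anticipation only, experienced burden, ethicality and cultural acceptability are never scored on the trial's own scale (0 of 40 trained participants), and this conflicts with the three-visit schedule in the text. The interviews, meant to inform barriers and retention, do not hear from people who withdraw: about 4 of 20 per arm at the retention target, counting failure to complete follow-up as not finishing.

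This rests on two readings: that the row-specific time point in Table 2 governs over the general sentence, and that finishing the trial excludes those who withdraw. If the general sentence governs, the scales are repeated after training and Table 2 is wrong; the correction is needed either way. The 72% benchmark (45% to 87% over the assumed retention range) assumes random selection and full agreement to be interviewed, so it illustrates the loss and does not predict it. No primary outcome, sample size or error rate depends on this scale.

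**What to change.** 1. Reconcile Table 2 with the Outcome measures text. Keep the baseline rating, add T_1m for the acceptability scales in the two trained arms, and report the change from baseline by arm. Since the arm is unknown at baseline, make clear that each training is rated separately there, so that the change refers to the training received.
2. Extend the interview invitation to participants who withdraw, made at the time they withdraw, within the same five per group. How many places they take can be left to the qualitative team; a fixed quota is a sampling preference.

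The cost is about eight 0–10 items at an existing visit, in a trial whose Discussion already acknowledges questionnaire burden, plus a revised invitation rule. The number of interviews is unchanged, and slightly fewer completers may be interviewed. The first change needs to be in place before participants reach the week-4 visit, because ratings missed then cannot be recovered.

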## Primary outcomes

### Feasibility data

The feasibility data (71) will be collected by the assistant research fellow.
•Recruitment rate and enrolment: The percentage of the number of participants recruited from the total number of participants screened over 1 year will be calculated. We aim to recruit 20 participants in each arm of the trial over 1 year in a single centre.•Compliance rate to training sessions: A research assistant providing training will record the number of training sessions attended by the participants (i.e., adherence rates). The adherence rates will be summarised as percentages. The reasons for non-compliance (e.g., adverse effects) will be documented. A targeted compliance rate of 80% will be considered acceptable.•Participant retention rate (dropout rates): The percentage of the allocated participants in each group who completed the follow-up assessment will be measured. A targeted retention rate of 80% will be considered acceptable.

### Safety data

The training administrator will record symptoms using the Discontinuation-Emergent Sign and Symptom (DESS) (93) checklist. The 43-item checklist includes emotional, behavioural, cognitive, and physical symptoms, and the participants will be required to compare their current status with their status prior to the training or the previous session.

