4. **Procedures:** Describe each of the procedures, activities, and/or processes used in the intervention, including any enabling or support activities.	Participants will be seated. Participants will be instructed to close their eyes, relax, and listen to the sound feedback. The participants will be instructed to minimise eye blinks, eye/head/neck movements, swallowing manoeuvres, and teeth clenching. The software programme will play a distinct tone when the brain activity of participants reaches the set threshold of infraslow magnitude at the pgACC. The RA-1 will be trained remotely by the Centre for Mindfulness (UCSD) to provide an MMT regimen in the trial. MMT involves instructing participants to focus on the sensation of each breath occurring at the tip of the nose. As a progression, the participants will be instructed to broaden their focus to the ‘full flow of the breath’, including bodily sensations. The participants will be instructed to acknowledge thoughts, feelings, and emotions as they arise without judgment and ‘simply return their attention back to the breath sensations’.
5. **Who provided** For each category of intervention provider (e.g., psychologist, nursing assistant), describe their expertise, background, and any specific training given.	A research assistant trained in delivering both interventions will administer the training.
6. **How** Describe the modes of delivery (e.g., face-to-face or by some other mechanism, such as internet or telephone) of the intervention and whether it was provided individually or in a group.	All participants will receive individual face-to-face training sessions.
7. **Where** Describe the type(s) of location(s) where the intervention occurred, including any necessary infrastructure or relevant features.	Interventions will be delivered in the School of Physiotherapy laboratory, University of Otago, Dunedin, New Zealand.
8. **When and how much** Describe the number of times the intervention was delivered and over what period of time, including the number of sessions, their schedule, and their duration, intensity, or dose.	The participants will undergo training for 12 sessions, four times a week, for three consecutive weeks. Each training session will last for a 30 min duration.

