### Interventions

Following the baseline assessment and group allocation, the participants will receive one of the active interventions or the usual care control group. The number of sessions and duration for both interventions will be identical. A trained research assistant will administer both active interventions. A research assistant will be trained to administer the study interventions. Both interventions will consist of 12 20-min sessions which will be administered in four consecutive sessions/week for three successive weeks. The interventions described in this study adhered to the Template for Intervention Description and Replication guide.

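### The unblinded trainer records participants' side effects on the symptom checklist, with no independent collection described, which risks under-reporting of a primary safety outcome

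*Protocol article*

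**What the plan says.** Safety sits under Primary outcomes. The Safety data section states: "The training administrator will record symptoms using the Discontinuation-Emergent Sign and Symptom (DESS". The checklist has 43 items covering emotional, behavioural, cognitive and physical symptoms, and participants rate themselves against an earlier status. The Discussion says it is recorded weekly.

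The Blinding section says that neither participants nor the intervention provider are blinded. Table 1 describes individual, face-to-face delivery over 12 sessions. The blinded research assistant is assigned the secondary outcomes (Outcome measures; Outcome assessor and blinding).

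The document names the trainer in two ways. Under Allocation concealment, "the ARF administers one of the active interventions to the participant". Under Interventions, "A trained research assistant will administer both active interventions", and Table 1 agrees: "A research assistant trained in delivering both interventions will administer the training".

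For the other primary outcomes, "The assistant research fellow will collect primary outcome measures throughout the study period" (Outcome measures) and "The feasibility data (71) will be collected by the assistant research fellow" (Feasibility data). The Feasibility data section also says: "A research assistant providing training will record the number of training sessions attended by the participants". It then says that reasons for non-compliance will be documented, with adverse effects as the example, but does not say by whom. On the interviews, the Qualitative study section says: "An assistant research fellow will coordinate with the investigators in conducting semi-structured in-depth interviews following the intervention". Interviews with Māori participants are assigned to a Māori researcher in the section on establishing relationships with Māori.

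**The concern.** Safety is Objective 2. The Discussion calls estimating side effects critical and says that this trial will be the first to provide signs and symptoms for this particular brief mindfulness protocol. Many checklist items are subjective, and a participant may soften such answers out of courtesy when the listener is the trainer. The trainer may also have expectations about the training and writes the record. Both pressures push towards fewer recorded symptoms, and a symptom that was never reported cannot be recovered at analysis.

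The same pressure could reach the reasons for missed sessions if the trainer is the one who asks. It could also reach the acceptability interview if the assistant research fellow is the trainer and takes part in the conversation.

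**Working it through.** The document gives no expected symptom rate, no under-reporting rate and no calculated sample size for the primary outcomes, so there is no planned figure to reproduce. The check has two parts: who does what, and how sensitive 20 participants per arm would be to unrecorded cases.

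**Roles**

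- Symptom checklist: the training administrator (Safety data). This holds whichever job title the trainer has.
- Attendance: the research assistant who provides training (Feasibility data).
- Reasons for non-compliance: recorder not named (Feasibility data).
- Primary outcomes in general, and the feasibility data: the assistant research fellow (Outcome measures; Feasibility data).
- Interviews: the assistant research fellow coordinating with the investigators (Qualitative study); a Māori researcher for Māori participants.
- Delivery of training: the assistant research fellow under Allocation concealment; a research assistant under Interventions, Table 1 and Feasibility data.
- Secondary outcomes: the blinded research assistant.

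The overlap between trainer and symptom recorder is explicit. The wider overlap, with the feasibility data and interviews, exists only if the Allocation concealment section is right about who trains.

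**Sensitivity at the planned size**

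Inputs: n = 20 per arm (Quantitative data analyses plan), giving 40 trained participants across the two active arms. The true per-participant rate p of a given symptom and the fraction m of affected participants who go unrecorded are both assumptions.

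Formula: P(at least one case recorded) = 1 − (1 − p(1 − m))^n.

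For p = 10%, n = 20:

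- m = 0: 1 − 0.90^20 = 0.878
- m = 25%: 1 − 0.925^20 = 0.790
- m = 50%: 1 − 0.95^20 = 0.642

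Range over assumptions:

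| n | p | m = 0 | m = 25% | m = 50% |
|---|---|---|---|---|
| 20 | 5% | 0.642 | 0.534 | 0.397 |
| 20 | 10% | 0.878 | 0.790 | 0.642 |
| 20 | 20% | 0.988 | 0.961 | 0.878 |
| 40 | 5% | 0.871 | 0.783 | 0.637 |
| 40 | 10% | 0.985 | 0.956 | 0.871 |
| 40 | 20% | 1.000 | 0.998 | 0.985 |

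Within one arm, under-recording matters most for the less common symptoms. For common symptoms, or ones shared by both active arms, at least one case would probably still be seen, although the estimated rate would be too low by the fraction m.

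**The case against.** The case for leaving the plan alone has real force. The checklist is fixed, the ratings are the participant's own, and weekly repetition gives several chances to report, whereas the calculation above treats each participant as recorded or missed once. Recording by the person present at the session is ordinary practice. Participants also have a route that avoids the trainer: satisfaction, usefulness and global perceived change are measured after training as secondary outcomes, which the blinded assistant collects, and self-report questionnaires go through Qualtrics, partly at home. Serious events, which drive the termination rule, are hard to hide out of politeness.

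Much of this stands, and it limits the size of the risk. It does not remove it. The participant's comparison is still given to the trainer, and the satisfaction ratings do not record symptoms.

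A reader might infer more: that one person trains participants, records every primary outcome and interviews them, so that the primary outcomes as a whole are biased in favour of the training. The document does not support that:

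- Only the Allocation concealment section makes the assistant research fellow the trainer.
- The fellow's stated part in the interviews is to coordinate with the investigators, which may mean scheduling.
- No recorder is named for reasons for non-compliance.
- Recruitment, attendance and retention are counts with little room for judgement, and the two 80% targets, for compliance and retention, rest on such counts.
- Nothing in the document makes checklist or interview results a criterion for going on to the full trial.

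**Conclusion.** The point holds in a limited form. The document expressly has the unblinded trainer record subjective symptoms and describes no independent collection, so side effects are at risk of under-reporting under either reading of the trainer's job title. Reasons for missed sessions may share that risk, depending on who records them. The interviews share it only if the assistant research fellow is the trainer and takes part in them.

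This is a risk and not a demonstrated bias, and its size is unknown. At an assumed 10% true rate, losing a quarter to a half of cases lowers the chance of recording at least one among 20 from 0.88 to between 0.79 and 0.64. The loss fractions are assumptions with no basis in the document. The change is worth making because it is cheap and the missing information cannot be recovered later.

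**What to change.** 1. Have participants complete the symptom checklist themselves in Qualtrics, together with a short item on the reason for any missed session. The trainer would see answers as needed for participant safety. Attendance can stay with the trainer.
2. Reconcile Allocation concealment, where the assistant research fellow delivers the training, with Interventions, Table 1 and Feasibility data, where a research assistant does. State who documents reasons for non-compliance.
3. If the assistant research fellow is the trainer, state that the acceptability interview is led by a team member who did not train that participant. Interviews with Māori participants are already assigned to a Māori researcher.

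Cost: two short forms on a platform already in use, a few extra minutes per participant and, if item 3 applies, some rescheduling of interviewers within the existing team.
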